**Methods/design:**

This study is a randomised, double-blind, parallel-arm trial in 98 participants with type 2 diabetes and a major depressive episode, according to DSM-IV criteria. We will assess whether light therapy improves depressive symptoms and insulin sensitivity, our primary outcome measures, and additionally investigate whether these effects are mediated by restoration of the circadian rhythmicity, as measured by sleep and hypothalamic-pituitary-adrenal axis activity. Participants will be randomly allocated to a bright white-yellowish light condition or dim green light condition. Participants will undergo light therapy for half an hour every morning for 4 weeks at home. At several time points, namely before the start of light therapy, during light therapy, after completion of 4 weeks of light therapy and after 4 weeks follow-up, several psychometrical, psychophysiological and glucometabolic measures will be performed.

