Insulin sensitivity will be evaluated at the baseline visit (T0) and the visit following light therapy (T4) in a subsample of 60 participants. Insulin sensitivity will be quantified using a hyperinsulinaemic-euglycaemic clamp procedure, the gold standard for the quantification of whole-body insulin sensitivity. This procedure quantifies the rate of exogenous glucose infusion required to maintain the plasma glucose concentration at euglycaemic levels in response to a fixed increase in the plasma insulin level. Because 80–90 % of the infused glucose is taken up by skeletal muscle under conditions of euglycaemic hyperinsulinaemia, insulin sensitivity measured with this procedure primarily reflects that of skeletal muscle [58]. The hyperinsulinaemic-euglycaemic clamp procedure is performed as previously described by DeFronzo and colleagues [59]. Briefly, participants will be admitted at our research unit following an overnight fast. They are placed in a semi recumbent position during the procedure. A cannula will be inserted into a vein in the antecubital fossa for infusion of glucose and insulin. Insulin (Novorapid 100 IU/ml; Novo Nordisk, Bagsvaerd, Denmark) will be continuously infused at a rate of 40 mU/m2*min, which creates a hyperinsulinaemic state, which will largely decrease endogenous glucose production by the liver. A contralateral dorsal hand or wrist vein will be cannulated and maintained at 50 °C to permit sampling of arterialised venous blood for bedside measurement of blood glucose concentrations (Yellow Springs Instrument 2300 STAT Analyser, Yellow Springs, Ohio, Unites States of America) every 5 min. Glucose (20 %) will be infused at a variable rate to maintain blood glucose levels at 5 mmol/L. When a stable blood glucose level of 5 mmol/L is achieved (minimally after 90 min of insulin infusion), the blood glucose level will be kept at this level for 30 min (steady state). At this point the glucose infusion rate equals the skeletal muscle glucose uptake. The M-value (expressed as the amount of glucose infusion in mol/kg*min) will be calculated over this steady state period as described previously [59]. Blood samples for measurement of plasma insulin concentrations will be obtained at several time points before and during insulin infusion.

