### Sample size

A previous study on the effects of light therapy on depression in elderly patients using a comparable protocol [30] showed that direct treatment effects of light therapy on depressive symptoms were moderate (effect size 0.50 Cohen’s d), and increased during follow-up (effect size 0.91 Cohen’s d), with one-sided testing. Power calculations were based on the expected moderate effect size and a conservative repeated measures correlation of 0.6, using conventional values for α (0.05) and β (0.20), and two-tailed tests with equal groups – the sample size aimed for will be 42 participants per treatment arm. Accounting for an attrition rate of 15 %, we derive at a total sample size of 98 participants.

The question whether light therapy alters insulin sensitivity in type 2 diabetes patients with depression will be tested in a subsample of 60 participants in total. A sample size of 30 participants per treatment arm is sufficient to detect a moderate effect (0.76 Cohen’s d) of light therapy on insulin sensitivity, with conventional values for α (0.05) and β (0.20), and two-tailed tests with equal groups, assuming a dropout rate of 10 %. The hyperinsulinaemic-euglycaemic clamp experiment will thus be performed in a subgroup of the participants and participation in this procedure will be optional. Participants with difficult venous access or medical conditions that impair the safety of the procedure will be excluded from participation in the hyperinsulinaemic-euglycaemic clamp experiment.

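### The clamp sample size labels d = 0.76 moderate where the same section uses that word for d = 0.50; 0.76 is only the unadjusted minimum detectable effect, and power at 0.50 depends on a contrast and correlation not fixed for the clamp

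*Protocol article*

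**What the plan says.** The abstract makes the clamp result co-primary: "We will assess whether light therapy improves depressive symptoms and insulin sensitivity, our primary outcome measures". The section on primary outcome measures fixes two clamps per participant: "Insulin sensitivity will be evaluated at the baseline visit (T0) and the visit following light therapy (T4) in a subsample of 60 participants".

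The Sample size section treats the two primary outcomes in consecutive paragraphs. For depression it cites a previous trial in which "direct treatment effects of light therapy on depressive symptoms were moderate (effect size 0.50 Cohen’s d"), and it sizes the trial on that effect with a repeated-measures correlation of 0.6. For the clamp it states that 30 per arm is "sufficient to detect a moderate effect (0.76 Cohen’s d) of light therapy on insulin sensitivity". The settings given there are a two-sided α of 0.05, 80% power, equal arms and 10% dropout. It gives no source for 0.76 and no correlation for the M-value.

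The Outcome measures section compares changes between conditions. The Statistical analyses section plans a repeated-measures mixed model and will evaluate both a treatment effect independent of time and a condition-by-time interaction. It does not say which of the two carries the clamp conclusion.

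**The concern.** One adjective covers two effect sizes, and the second is about half as large again as the first (0.76 / 0.50 = 1.52). No outside convention is needed to see the conflict, because the section attaches the word to 0.50 itself.

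What is at stake is how a non-significant clamp result would be read. Someone who relies on the sample size statement could take it as evidence against a moderate effect in the sense the section first gives the word. Whether the design supports that depends on which contrast is tested and on how strongly T0 and T4 M-values correlate. Neither is fixed for the clamp, and one of the two effects the plan names is very insensitive with only two clamp visits.

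**Working it through.** **Inputs from the article.** 30 per arm, 10% dropout, two-sided α = 0.05, β = 0.20, 1:1 allocation. Evaluable per arm: 30 × 0.9 = 27. **Assumed here:** equal SD of the M-value at T0 and T4, d expressed in units of that SD, no baseline difference in expectation, and a T0–T4 correlation r of 0.5 to 0.8.

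**1. Reproducing 0.76.** The unadjusted minimum detectable effect is (1.960 + 0.842) × √(2/27) = 2.802 × 0.272 = 0.762 by the normal approximation, or 0.777 by the t distribution with 52 df. Conversely, at d = 0.76, 0.76 × √(27/2) = 2.792 and Φ(2.792 − 1.960) = 79.7%; the noncentral t gives 78.2%. The stated figure therefore reproduces with no correlation used.

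**2. Basis used for depression.** With d = 0.50 and variance factor 1 − 0.6² = 0.64, the effective d is 0.50/√0.64 = 0.625. The t-based requirement is 41.2, rounded up to the stated 42 per arm. This reproduction relies on the correlation; the clamp reproduction does not.

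**3. Unadjusted power at d = 0.50.** 0.50 × √(27/2) = 1.837 and Φ(1.837 − 1.960) = 45.1%; the noncentral t gives 43.8%. An unadjusted comparison would need 64 evaluable per arm for 80%. The expected 95% CI half-width is 2.007 × 0.272 = 0.55 SD.

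**4. Power at d = 0.50 for contrasts that use T0.** The effective standardised effects are:
- change from T0 to T4 (equivalent to condition-by-time with two visits): 0.50/√(2(1 − r));
- T4 adjusted for T0: 0.50/√(1 − r²);
- treatment averaged over T0 and T4: 0.25/√((1 + r)/2). The expected difference is zero at T0 and 0.50 at T4, so its mean is 0.25.

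Power by noncentral t, 27 per arm:

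| Assumed r | Change / condition-by-time | T4 adjusted for T0 | Averaged over T0 and T4 |
|---|---|---|---|
| 0.5 | 44% | 55% | 18% |
| 0.6 | 52% | 62% | 17% |
| 0.7 | 64% | 71% | 16% |
| 0.8 | 81% | 85% | 16% |

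**5. Detectable effect and precision for T4 adjusted for T0.** The detectable d is 0.777 × √(1 − r²): 0.67 at r = 0.5, 0.62 at r = 0.6 and 0.47 at r = 0.8. The CI half-width at r = 0.6 is 0.55 × 0.8 = 0.44 SD.

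**The case against.** The strongest reply is that nothing is miscalculated and nothing is hidden. The 0.76 stands in the text beside the adjective, its inputs are all stated, and it reproduces. This is right: a reader might infer an arithmetic error or a wrong number of participants, and the document supports neither.

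Second, 44% is not the power of the planned analysis. The plan compares changes and fits a repeated-measures model, so the T0 clamp already enters; only the sample size calculation leaves it out. This also stands. A flat claim that this primary outcome has 44% power goes too far. That figure belongs to the unadjusted test, which is also the low end of the range for the change contrast.

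Third, the article presents the question as untested, so with no prior estimate it is legitimate to quote the detectable effect for a feasible number of optional clamps. I accept that. It is a reason to describe 0.76 as a detectable effect, which the text does not do.

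Fourth, the article draws its conclusions only from a positive result and nowhere says it will read a null as absence of effect. That is true, so the misreading is a risk and not a stated intention.

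Relabelling 0.76 as large would not help: it swaps in another label that the document does not define. Moving from 0.76 to 0.78 is only the difference between the normal and t calculations.

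One part of the concern is untouched by these replies. If T0 is a response in the model, as a condition-by-time term for the clamp requires, the time-independent treatment effect is diluted by a visit at which no effect can exist.

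**Conclusion.** The point holds as a conflict of labelling with a consequence for the analysis. Within one section the same word describes 0.50 and 0.76, and the clamp figure is an unadjusted minimum detectable effect presented as if it were a moderate one.

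At d = 0.50 with 27 evaluable per arm, power is about 44% unadjusted, 44% to 81% for condition-by-time, 55% to 85% for T4 adjusted for T0, and under 20% for the time-averaged treatment effect. The ranges rest on an assumed r of 0.5 to 0.8 and equal variances at the two visits; the last figure also takes independence of time to mean averaging over both clamps. The conventional 80% is reached only near the top of the correlation range, so the statement as worded cannot be relied on for an effect of 0.50.

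A reader might go further and infer that any null clamp result would be uninformative. The calculations do not show that. With adjustment and a high correlation the interval could be narrow enough to exclude 0.50. The interval, not the significance test, should settle it.

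**What to change.** 1. In the Sample size section, delete the adjective and describe 0.76 as the minimum detectable effect of an unadjusted comparison with 27 evaluable per arm.
2. State the power at d = 0.50 beside it: about 44% unadjusted, and 55% to 85% for the adjusted contrast over r = 0.5 to 0.8, with the correlation marked as an assumption.
3. Name one primary clamp contrast before unblinding: the between-arm difference in T4 M-value adjusted for T0 M-value, by ANCOVA or a baseline-constrained mixed model. At r = 0.6 and d = 0.50 this gives about 62%, against 52% for condition-by-time and 17% for the time-averaged effect.
4. Commit to reporting a non-significant clamp result with its confidence interval, and not as absence of a moderate effect.

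The cost is a less favourable stated sensitivity and a small amendment to the analysis, which must be made while the data are still blinded. No additional clamps or participants are needed.

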### Statistical analyses

Data will be analysed using SPSS (version to be determined). Participant and baseline characteristics across treatment groups will be compared using analysis of variance (ANOVA) and chi-squared statistics. Analyses of our primary outcome measures will be performed on the basis of intention to treat. The superiority of the bright white-yellowish light condition compared to dim green light condition will be tested using a repeated measures mixed models design. Both treatment (independent of time) and condition*time interaction effects will be evaluated. Repeated measures logistic regression will be applied to test differences in depression remission rates. Preacher and Hayes mediation analysis will be performed to test whether the effects of light therapy are mediated by restoration of the circadian rhythmicity. Post hoc analyses of this study may include subgroup or discriminant analysis to test if participant characteristics can be identified that predict positive effects of light therapy, such as baseline depression severity, baseline depressive symptoms profile, baseline insulin sensitivity, baseline HbA1c, chronotype, or baseline insomnia severity, seasonality of depression and time of year at which the participant was included in the study.

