#### Primary outcome measures

Depressive symptoms will be assessed by the self-report version of the Inventory of Depressive Symptomatology (IDS) (T0, T1, T2, T3, T4, T8) [57]. The IDS allows for profiling of depression, as the questionnaire discriminates directions of the weight, appetite, sleep and psychomotor symptoms, and can be used to determine depression severity. Scores between 14 and 25 indicate mild depression; scores between 26 and 38 indicate moderate depression; scores between 39 and 48 indicate moderate to severe depression; and scores of 49 and greater indicate severe depression. A reduction of 50 % or greater of the baseline depression score is regarded as a clinically significant reduction in depressive symptoms. Depression remission is *a priori* defined as an IDS score of 13 or less.

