#### Circadian mediating factors

Mediating factors that reflect circadian rhythmicity will include diurnal HPA axis activity, objective accelerometer measures of sleep duration and subjective measures of sleep duration and quality.

Diurnal HPA-axis activity is assessed by free cortisol assessment using six saliva samples per day (T0, T4, T8). The morning cortisol awakening responses will be assessed by four saliva samples in the morning: after awakening, plus 30 min, plus 45 min and plus 60 min. Cortisol levels in the evening will be obtained from two saliva samples in the evening at 10 and 11 pm. Saliva samples will be collected at home, using cotton swaps (Salivette, Sarstedt, Nümbrecht, Germany) that will be stored in the refrigerator. Participants will bring the samples with them to the research facility where the saliva will be centrifuged and stored at −80 °C for analysis.

Objective measures of sleep will be obtained using a microelectromechanical system (GENEActiv, Activeinsights Ltd, Kimbolton, United Kingdom), an accelerometer that can reliably measure sleep-wake behaviour [64] and will be worn for one week continuously. Estimates of sleep parameters will be obtained from these data using a previously validated algorithm [64].

Subjective sleep parameters will be scored using the Pittsburg Sleep Quality Index (T0, T4, T8) [65], the Insomnia Severity Index (T0, T2, T4, T8) [66, 67] and a sleep diary (T0, T1, T2, T3, T4, T8) [68].

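### Mediation of the IDS effect through self-rated sleep has sleep content on both sides, so a sleep-only effect could be read as circadian mediation of an antidepressant effect

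*Protocol article*

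**What the plan says.** The third hypothesis, at the end of the Background, is that effects on depressive symptoms and on insulin sensitivity run through restored circadian rhythmicity, indexed by the sleep-wake pattern and HPA axis activity. The Statistical analyses section names the Preacher and Hayes method and says that "mediation analysis will be performed to test whether the effects of light therapy are mediated by restoration of the circadian rhythmicity". It does not say which mediator variables, time points or version of the outcome score enter the model.

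Under Primary outcome measures, the self-report IDS is taken at T0, T1, T2, T3, T4 and T8. One reason given for choosing it is that "the questionnaire discriminates directions of the weight, appetite, sleep and psychomotor symptoms".

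Under Circadian mediating factors, the mediators "will include diurnal HPA axis activity, objective accelerometer measures of sleep duration and subjective measures of sleep duration and quality". Self-rated sleep comes from the sleep quality index (T0, T4, T8), the Insomnia Severity Index (T0, T2, T4, T8) and a sleep diary (T0 to T4, T8). Cortisol is sampled at T0, T4 and T8. An accelerometer is worn continuously for one week.

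**The concern.** In a mediation model the second path is the regression of outcome on mediator, adjusted for treatment. If both contain self-rated sleep, part of that path is one construct regressed on itself. Suppose light improves sleep and leaves mood, interest, energy and the other symptoms unchanged. The insomnia index falls, and the IDS falls through its own sleep items. The model can then return a significant indirect effect, and under the article's wording this would be reported as circadian mediation of an antidepressant effect.

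The stake is interpretation. The Discussion part of the Abstract and the Conclusions both say that support for the circadian role may guide further development of chronobiological treatment. The Conclusions extend this to patients with sleep disorders but no depression. A finding that reflects shared sleep content would be a weak basis for either.

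**Working it through.** **The plan's own figure.** No sample size is given for the mediation analysis, so the check uses the 42 per arm from the Sample size section. That figure reproduces with d = 0.50, correlation 0.6, two-sided 0.05, 80% power and six repeated measures (six is inferred from the IDS schedule): 2 × ((1.960 + 0.842)/0.5)² × (1 + 5 × 0.6)/6 = 62.8 × 4/6 = 41.9, so 42. The analysed total is 84.

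**Assumptions, none of them in the article.**
- Treatment shifts true sleep by 0.5 SD. It has no effect on other symptoms, and sleep has no link to them.
- The mediator and the IDS sleep items each load 0.8 on true sleep.
- The sleep items make up a share w of the IDS score.
- Mediation is declared when both paths have p < 0.05. This joint-significance test stands in for the Preacher and Hayes bootstrap.

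**First path (treatment to mediator).** The effect on the mediator is 0.8 × 0.5 = 0.4 SD. The noncentrality is 0.4 × √(42/2) = 1.83, so power is about 0.45.

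**Second path (mediator to IDS).** The correlation from overlap alone is r = w × 0.8 × 0.8 / √(w² + (1 − w)²). At w = 0.14 this is 0.0896/0.871 = 0.10. At w = 0.20 it is 0.128/0.825 = 0.16. The noncentrality is about r × √84.

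| Sleep share w | r | Second-path rate | Product with 0.45 | Simulated (4,000 trials) |
|---|---|---|---|---|
| 0 (items removed) | 0 | 5% | 2.2% | 2.2% |
| 5% | 0.03 | 6% | 2.7% | 2.6% |
| 10% | 0.07 | 10% | 4.5% | 4.7% |
| 14% | 0.10 | 16% | 7.0% | 6.2% |
| 20% | 0.16 | 30% | 13.3% | 12.2% |

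The hand approximation and the simulation agree closely. Inflation is small up to about a 10% share and grows quickly beyond it.

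**Sensitivity to the assumptions.**
- With a sleep effect of 0.8 SD, the simulated rates at 14% and 20% are 12.7% and 23.8%.
- With no measurement error (loadings of 1) and a 0.5 SD sleep effect, the rates at shares of 0, 5, 10, 15 and 20% are 3, 5, 9, 20 and 36%. Here treatment also improves other symptoms by 0.5 SD, not through sleep; 0, 5, 10, 15 and 19% of the IDS effect is then labelled as mediated.

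**What removing items does not do.** In the no-error setting with the sleep items removed, suppose sleep and the other symptoms share a same-visit residual correlation of 0.3 or 0.5 without any causal path. Apparent mediation is then 49% or 63%. This is ordinary mediator-outcome confounding, separate from the overlap, and it can be larger.

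**Where the overlap stops.** Salivary cortisol shares no items with the IDS. The clamp M-value has no sleep content: with 27 per arm and no residual correlation, apparent mediation is 1.5%. Accelerometer sleep duration is not a questionnaire score, so its overlap with the IDS is through the construct only.

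**The case against.** The strongest objection is that the simulated result is not false. The Background lists sleep disturbance among the symptoms of major depression. A treatment that improves sleep lowers the IDS total, and for the total that is a genuine, if small, indirect effect. This stands. It is why the rates above are called apparent mediation, and why the point concerns what the result may be said to show. Neither the IDS nor the method is at fault.

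A reader might infer more than the documents support, in four ways:

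- **That the whole mediation analysis is circular, or positive by construction.** Cortisol and the M-value are outside the overlap. Even at a 20% share, almost nine in ten simulated trials in the main setting show no mediation.
- **That mediator and outcome are modelled at the same visit, so direction cannot be separated.** All listed mediator times are also IDS times, but the article prescribes no pairing. The T2 insomnia index and the T1-T3 diary precede the T4 IDS, and the T4 mediators precede the T8 IDS.
- **That nothing timing-related is recorded.** The summary sentence names only sleep duration and quality, yet a week of sleep-wake recording and a diary are collected, and "Cortisol levels in the evening will be obtained from two saliva samples in the evening at 10 and 11 pm". Timing may be derivable.
- **That missing model details are an error.** A condensed article may leave time points and derived variables to the full plan. The overlap is different, because it follows from instruments that the article itself names.

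**Conclusion.** The concern holds for the IDS outcome and mainly for the self-rated sleep mediators. As written, a significant indirect effect there cannot be told apart from an effect on sleep alone. The documents do not fix the size. Under the main assumptions, apparent mediation is about 3-5% of trials at a 5-10% sleep share and 6-12% at 14-20%, against about 2% without overlap. A larger sleep effect or more reliable scales raise it. If the sleep share is small, so is the problem.

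Hypothesis 3 is mechanistic. The randomised comparison on the IDS, the insulin sensitivity comparison and the sample size are untouched. The change is worth making because it is cheap and makes the hypothesis interpretable.

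**What to change.** 1. For every mediation model with a sleep mediator and the IDS as outcome, also fit the model with the IDS minus its sleep items. Claim mediation of the antidepressant effect only if the indirect effect persists there.
2. Where data exist, use a mediator measured before the outcome: the T2 insomnia index or T1-T3 diary for the T4 IDS, and T4 mediators for the T8 IDS. Item removal does not cure same-visit confounding. Lagging sets the time order but does not exclude common causes.
3. Either derive a sleep-timing or regularity variable from the accelerometer week and name it as a circadian mediator, or word the conclusion as mediation by sleep and cortisol.

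No new data are needed. The cost is slightly lower reliability of the shortened scale and a few extra models. The full IDS remains the primary outcome for the treatment comparison.

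### Discriminant analysis, named for finding who benefits from light therapy, identifies who improves under either lamp; a lamp-by-characteristic interaction would answer the question asked

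*Protocol article*

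**What the plan says.** The protocol article, Statistical analyses, closes with an optional analysis: "Post hoc analyses of this study may include subgroup or discriminant analysis to test if participant characteristics can be identified that predict positive effects". The effects meant are those of light therapy. The candidates are given as examples: "baseline depression severity, baseline depressive symptoms profile, baseline insulin sensitivity, baseline HbA1c, chronotype, or baseline insomnia severity, seasonality of depression and time of year" of inclusion. That makes eight, and the list is left open.

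The only interaction named in the section belongs to the main comparison: "Both treatment (independent of time) and condition*time interaction effects will be evaluated". No term combining lamp with a baseline characteristic is mentioned.

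Two facts from elsewhere in the article matter. Under Primary outcome measures, a clinically significant reduction and remission are both defined on the depression score, so ready-made outcome groups exist for a discriminant analysis. Under Randomisation, allocation to the two lamps is 1:1, so a concurrent control group exists within every level of every characteristic.

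**The concern.** The stated aim concerns the effect of light therapy. That effect is a contrast between lamps, so a predictor of it is a characteristic over which the contrast changes. Discriminant analysis looks for variables that separate predefined groups. If the groups are improved and not improved, and lamp is not in the analysis, the variables found are prognostic. Baseline severity, insomnia severity, seasonality and time of year could all plausibly relate to improvement under either lamp.

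The post hoc label lowers the weight that a result deserves. It does not change what the method estimates. At stake is a secondary statement about which patients to select for light therapy. Such a statement could rest on a characteristic that merely marks people who get better anyway, although the randomised control arm could have told the two apart.

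**Working it through.** **Inputs from the article.**
- Effect size, Sample size section: "direct treatment effects of light therapy on depressive symptoms were moderate (effect size 0.50 Cohen’s d".
- Correlation, same section: "Power calculations were based on the expected moderate effect size and a conservative repeated measures correlation of 0.6".
- Error rates and size per arm, same section: "conventional values for α (0.05) and β (0.20), and two-tailed tests with equal groups – the sample size aimed for will be 42 participants per treatment".
- Number of depression measurements, Primary outcome measures: "self-report version of the Inventory of Depressive Symptomatology (IDS) (T0, T1, T2, T3, T4, T8", that is, six.
- Attrition, Sample size section: "Accounting for an attrition rate of 15 %, we derive at a total sample size of 98 participants".
- Baseline insulin sensitivity: measured in a subsample of 60.

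**Step 1: reproduce the 42 per arm.** The article does not give its formula. For two means without repeated measures, n = 2 × ((1.960 + 0.842)/0.50)² = 62.8 per arm. The variance factor for the mean of six measures with correlation 0.6 is (1 + 5 × 0.6)/6 = 0.667. The product is 62.8 × 0.667 = 41.9, so 42. A baseline-adjusted factor, 1 − 0.6² = 0.64, gives 40.2, so 41. Either reading supports about 80% power at 42 per arm. For the total, 98 × 0.85 = 83.3, close to 2 × 42 = 84.

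**Step 2: overall power.** Standard error of the lamp difference = √(2 × 0.667/42) = 0.178. Power = Φ(0.50/0.178 − 1.96) = Φ(0.846) = 0.80.

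**Step 3: discriminant analysis without a treatment term.** Suppose a characteristic shifts the outcome equally under both lamps, so that it modifies nothing. Test it as a predictor of outcome within the bright-light arm, split 21 and 21. The standard error is √(2/21) = 0.309 outcome SD.
- Shift of 0.5 SD: Φ(0.5/0.309 − 1.96) = Φ(−0.34) = 0.37. A simulation of 5,000 trials with random splits and t-tests gave 35%.
- Shift of 0.8 SD: Φ(0.8/0.309 − 1.96) = Φ(0.63) = 0.74. The simulation gave 71%.
- An interaction test on the same simulated data flagged the same characteristic in about 5% of trials, its nominal rate.

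The shifts of 0.5 and 0.8 SD are illustrative assumptions; the article gives no prognostic strengths.

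**Step 4: subgroups, if read by separate significance.** Let the true effect be the same in everyone and split the sample into equal halves. The standard error in a half is 0.178 × √2 = 0.252, so power is p = Φ(0.50/0.252 − 1.96) = Φ(0.02) = 0.51. The chance that exactly one half is significant is 2p(1 − p) = 2 × 0.51 × 0.49 = 0.50. In simulation with eight independent even splits, at least one such contrast appeared in about 90% of trials. With no true effect at all, the figures were 9% per characteristic and 38% for at least one of eight.

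**Step 5: what interaction tests would deliver.** With a 50:50 split, the standard error of the interaction is twice that of the main effect: 2 × 0.178 = 0.356. For an interaction as large as the main effect (0.50), power = Φ(0.50/0.356 − 1.96) = Φ(−0.56) = 0.29. Eight independent unadjusted tests at 0.05 give at least one false positive with probability 1 − 0.95⁸ = 0.34.

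**The case against.** The strongest reply is that the article commits to very little. The analyses are optional, offered as alternatives and labelled post hoc. No hypothesis, sample size or conclusion depends on them. How subgroups would be tested is commonly left to an analysis plan that is not shown. All of this stands, and it limits the point to a minor one.

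A reader might infer that subgroup analysis, like discriminant analysis, is incapable of distinguishing effect modifiers from prognostic factors. The documents do not support that. Comparing the randomised arms within strata and testing the difference by interaction does distinguish them, and the article does not exclude it. Nor does it say that scores will be split or that strata will be read by separate p-values. The 50% and 90% figures therefore describe one possible way of reading subgroups, not a stated plan.

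The 34% also belongs to unadjusted interaction tests, that is, to the proposed replacement, and is not evidence against the present wording. The eight characteristics are unlikely to be independent: severity, symptom profile and insomnia overlap. That would lower the any-of-eight rates, while the open list and a second primary outcome would raise them.

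What the reply does not remove is the choice of discriminant analysis. The article names that method for this aim, and it fits the aim only if lamp enters the analysis.

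**Conclusion.** The point holds as a minor one. As named, discriminant analysis of outcome groups does not answer whether a characteristic predicts the effect of light therapy. Subgroup analysis answers it only with a test of the lamp difference across subgroups, which the article does not mention.

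The size depends on assumptions. With the illustrative shifts of 0.5 and 0.8 SD, a purely prognostic characteristic would be flagged within the bright-light arm in about 35% and 71% of trials, against about 5% with an interaction test. This assumes that the discriminant analysis uses outcome groups without a lamp term; the article does not specify its groups or arms. If subgroups were read by separate significance, with about 80% overall power and equal halves, a uniform effect would look confined to one half about 50% of the time.

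A reader might go further and expect the trial to publish a spurious responder profile. The article gives no basis for predicting that: the analyses may not be run, and they are already marked post hoc. No primary conclusion is affected.

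**What to change.** In Statistical analyses, replace the discriminant analysis with a lamp-by-characteristic interaction added to the planned mixed model, using both arms. The term should match the treatment contrast used for the main comparison. If the baseline score remains among the repeated outcomes, that means a three-way term with time. Any subgroup results should be presented alongside the interaction and not judged by their own p-values.

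Keep scores such as baseline depression, HbA1c and insomnia severity continuous. Close the list of characteristics, and report the interaction estimate with its 95% interval for every one of them, labelled exploratory.

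The cost is a change of wording; no data collection changes. The drawback is that most results will be inconclusive. Power is about 29% even for an interaction as large as the main effect (50:50 split, 42 per arm). Baseline insulin sensitivity, available in at most 60 participants, will be less informative still. Eight unadjusted independent tests carry about a 34% chance of at least one false positive, so the interaction results should be read as hypothesis-generating too.
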